### Duration of trial

The study will require 24 months to complete: 6 months for recruitment and 18 months to complete follow-up, data collection and analysis.

### Blinding

Given the nature of the intervention, it is not possible to blind the patient to their trial group. However, the statistician analysing the RCT data will be blinded to the study group.

### Ethical considerations

The REACT study protocol has been approved by the Alfred Health Human Research Ethics Committee (HREC), South Eastern Sydney and Illawarra Area Health Service HREC and the University of New South Wales HREC.

### Trial inclusion and exclusion criteria

Patients will be included if they: are aged 16 years or above; have a mobile phone; are heterosexual men (reported sexual contact only with female partner/s in the last 12 months)/MSM (reported sexual contact with male partner/s in the last 12 months)/or women; have a diagnosis of chlamydia infection (diagnosed by NAAT); and reside in a jurisdiction serviced by the sexual health clinic and plan to stay in that jurisdiction for the next six months. Patients will be excluded if they: are unwilling or unable to comply with all the requirements of the protocol; cannot speak English; are HIV positive or a current sex worker.

### Recruitment

A total of 600 participants (200 MSM, 200 women and 200 heterosexual men) diagnosed with chlamydia are required. The trial will be advertised by postcards left in the waiting room or provided to patients at the time of chlamydia testing or treatment. All positive chlamydia results will be reviewed by study nurses based at each of the clinics. Among potentially eligible patients, the nurse will contact the patient by telephone and let them know of their chlamydia diagnosis and for those not already treated, recommend they come to the clinic for treatment. During the call the nurse will give a brief overview of the study and asked the patient for permission to pass on their contact details to a member of the research team. If the patient agrees, a member of the research team will then contact the patient to explain the trial requirements and undertake a verbal consent process.

### Randomisation

Eligible patients will be randomised to the intervention or control strategies using a minimisation approach. This will maximise the balance across the risk groups (MSM, women and heterosexual men). Computer generated randomisation codes, stratified for risk group will be produced by a statistician and sealed in opaque envelopes. Once consent has been given, the research team member will select the next randomisation envelope according to the risk group of the patient and inform the patient which group they have been assigned to – the home or clinic group.

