## Methods/Design

### Study design/setting

This is a non-blinded, randomised controlled trial (RCT) where individuals are randomised in a 1:1 ratio to an SMS reminder and home-based, self-collected samples (home group) or an SMS reminder and clinic testing (clinic group). The trial is being conducted in two Australian sexual health clinics (Melbourne and Sydney Sexual Health Centres). The study is diagrammatically represented in Figure 1.

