### Analysis

#### Chlamydia retesting and repeat positive test rates

The final analysis of primary and secondary outcomes will be performed at the conclusion of the trial. Patient baseline characteristics will be compared by randomised group as appropriate but no formal statistical tests will be undertaken. Analyses will be conducted using STATA statistical analysis software. An intention-to-treat approach will be taken.

In the initial analysis, the percentage of individuals who returned will be cross tabulated by randomised group. The analysis will determine the effect of the intervention on primary and secondary outcomes overall and between risk groups (MSM, women and heterosexual men). The primary analysis will be retesting rates between 1-4 months after a chlamydia diagnosis. Per protocol analyses will include: i) among the home-testing arm: the percentage who retested at home compared with the clinic, and the median time to retest among those who tested at the clinic versus home; ii) in each arm: the median time to retest (overall and in those who retested positive); and iii) factors associated with repeat positivity among those who retested at 1-4 months.

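### The allocation is labelled minimisation but described as stratified envelope randomisation, and the overall comparison described does not use the risk-group strata

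*Protocol article*

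**What the plan says.** The Randomisation section of the protocol article opens with "Eligible patients will be randomised to the intervention or control strategies using a minimisation approach" and gives the purpose: "This will maximise the balance across the risk groups (MSM, women and heterosexual men"). Risk group is the only factor named. The same paragraph then sets out the procedure: "Computer generated randomisation codes, stratified for risk group will be produced by a statistician and sealed in opaque envelopes". After consent, "the research team member will select the next randomisation envelope according to the risk group of the patient" and tells the patient the result.

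Under Study design/setting, "individuals are randomised in a 1:1 ratio", and recruitment is at two sites: "The trial is being conducted in two Australian sexual health clinics". Clinic is not named as a balancing factor.

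Under Analysis (Chlamydia retesting and repeat positive test rates), the text says "In the initial analysis, the percentage of individuals who returned will be cross tabulated by randomised group". It then says that effects will be determined overall and between the three risk groups. It does not say whether the overall comparison takes account of risk group or clinic.

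**The concern.** Minimisation ordinarily assigns each patient from the running totals of those already enrolled. A sealed list is fixed before anyone enrols. The paragraph presents both as the method, so a reader cannot tell how the sequence is produced.

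This matters most for predictability. The trial is not blinded, the research team takes consent, and a team member opens the envelope and announces the arm, so earlier assignments within a risk group can be known to the team. With one factor and no random element, minimisation tosses a coin when the arms are level and forces the next assignment, exactly as blocks of two would. A list with a less regular structure does not have that weakness. The label therefore affects how well the next assignment is concealed.

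The second matter is efficiency. When allocation is stratified by a prognostic factor, an overall comparison that ignores the factor overstates the standard error somewhat. The article's own background figures suggest that risk group is prognostic. Under Chlamydia retesting, 30-120 day retest rates at Australian sexual health services were 8.6% in MSM, 11.9% in heterosexual men and 17.8% in women.

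**Working it through.** **The two descriptions.** The label (minimisation) implies assignment from running totals. The procedure (codes made in advance by a statistician, stratified by risk group, sealed, next envelope taken within the group) is stratified randomisation from a fixed list. With risk group as the only factor, a minimised sequence depends only on earlier assignments in that group. It could therefore be written out beforehand. The two statements can be made compatible, but only if the list is a balanced one, and the text does not say so.

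**The plan's own figures.** Inputs from Sample size calculation: 40% against 60%, 80% power. Two-sided alpha of 0.05 is assumed because none is stated. Pooled-variance formula per arm:

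n = [1.960 × √(2 × 0.5 × 0.5) + 0.842 × √(0.24 + 0.24)]² / 0.20² = 96.9, so 97 per arm and 194 per risk group, as stated.

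For 52% against 40%, 300 per arm gives 84.0% power (540 in total would suffice), consistent with the stated minimum of 80%. None of this depends on the allocation method.

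**Gain from stratifying by risk group.** With equal risk groups split 1:1, the crude and Mantel-Haenszel risk differences coincide, and only the variance differs. Ratio = mean of p(1−p) over the groups, divided by p̄(1−p̄).

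| Clinic-group rates | Mean p(1−p) | p̄(1−p̄) | Ratio | Variance removed |
|---|---|---|---|---|
| 30/40/50% (assumed) | (0.21 + 0.24 + 0.25)/3 = 0.2333 | 0.24 | 0.972 | 2.8% |
| 25/40/55% (assumed) | (0.1875 + 0.24 + 0.2475)/3 = 0.2250 | 0.24 | 0.938 | 6.2% |
| 8.6/11.9/17.8% (article background) | (0.0786 + 0.1048 + 0.1463)/3 = 0.1099 | 0.1277 × 0.8723 = 0.1114 | 0.987 | 1.3% |

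The last row comes from years before this trial and lies far below the 40% planned for here, so it serves only as a lower marker. On the standard error, the two assumed cases give 1 − √0.972 = 1.4% and 1 − √0.938 = 3.2%.

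**Simulation.** 20,000 runs, 100 per arm in each risk group, true difference 12 points for power:

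| Clinic-group rates (assumed) | Type I error, crude / stratified | Power, crude / stratified |
|---|---|---|
| 40/40/40% | 5.1% / 5.1% | 84.6% / 84.3% |
| 30/40/50% | 4.9% / 5.1% | 85.1% / 85.3% |
| 20/40/60% | 3.5% / 4.6% | 86.2% / 88.3% |

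The crude test does not exceed its nominal level where the strata differ. It loses about 0.2 to 2 points of power.

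**Chance imbalance by clinic.** Assume a 50:50 recruitment split and a 15-point difference between clinics in retesting; neither figure is in the article. SD of the between-arm difference in clinic share = √(2 × 0.25/n per arm).

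- Overall: √(0.5/300) = 0.041. Shift: 1.96 × 0.041 × 15 = ±1.2 points.
- One risk group: √(0.5/100) = 0.071. Shift: 1.96 × 0.071 × 15 = ±2.1 points.

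For scale, the 95% half-width at the planned rates is 1.96 × √((0.24 + 0.2496)/300) = 7.9 points overall and 1.96 × √(0.48/100) = 13.6 points in a risk group.

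**The case against.** The strongest reply is that nothing of substance is wrong. With a single factor the label and the procedure can be reconciled, and the operational steps are clear enough to follow. Either way the balancing factor is risk group, so the implication for the analysis is the same. This stands to the extent that one should not infer that the two descriptions are impossible together, or that the randomisation is invalid. It does not remove the need to state one method, because the two labels imply different degrees of predictability.

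A reader might also infer that the allocation ignores risk group. The text says the opposite: the codes are stratified by it and the envelope is chosen by it. Nor is the stratification made redundant by the quota of 200 per group, which fixes the size of each group and not the balance of arms within it.

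On the analysis, the cross-tabulation is called initial, effects between risk groups are planned, and adjustment of the overall comparison is commonly specified in an analysis plan that is not shown. That is fair. Stratifying is therefore a recommended gain, already met if that plan contains it.

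On clinic, chance imbalance under randomisation is not bias, and the usual standard error covers it. The article gives no sign that retest rates differ between the sites, and reminders are routine at both. Different pathology providers do not bear directly on whether a patient retests. Leaving clinic out of the allocation is therefore a legitimate choice and not an error.

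**Conclusion.** The point holds in a limited form. The Randomisation section gives a label and a procedure that do not match as written, and this should be corrected. It follows from the text alone and needs no assumption. Minimisation is probably the wrong word for stratified randomisation.

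The overall comparison as described does not use the strata that the allocation does use. The cost is small: about 3% to 6% of the variance under assumed rates of 30/40/50% to 25/40/55%. The documents do not support the stronger reading that an unstratified comparison would be invalid; it errs slightly on the conservative side.

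Adding clinic to the allocation is optional. The shifts of ±1.2 and ±2.1 points rest on an assumed 50:50 split and an assumed 15-point clinic difference, and are small beside the 12- and 20-point effects the trial is sized for. All stated sample sizes and power figures are unaffected.

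**What to change.** 1. In the Randomisation section, state the one method used. If envelopes were used, delete minimisation and say briefly how the list is generated so that the next assignment cannot be predicted, for example permuted blocks of varying size within risk group. Finer detail can stay in the full protocol.
2. Make the overall primary comparison stratified by risk group, for example a Mantel-Haenszel risk difference, with clinic added as a stratum or covariate. Six risk-group-by-clinic strata would average 600/6 = 100 patients, so sparse cells are unlikely unless recruitment is very uneven. If the analysis plan already does this, a cross-reference is enough.
3. If allocation has not started, consider stratifying the envelopes by clinic as well. If it has, leave the allocation alone and handle clinic in the analysis.

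The cost is a wording correction, a stratified analysis in place of a crude one on information that should be known for every patient, and, for the optional step, six envelope sequences instead of three. No additional patients are needed.

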### Intervention (home testing) arm

The home-collection kit will contain the collection device, illustrated collection instructions, laboratory request form and pre-paid envelope. The collection devices will vary according to the patient’s risk group as follows: for heterosexual men the collection device will consist of a sponge-based urine collection device (UriSWAB®, Copan Diagnostics, CA, USA); for women the collection device will consist of a swab for lower vaginal self-collection and for MSM two collection devices will be provided: (i) a swab for rectal self-collection; and (ii) a UriSWAB for first-pass urine collection.

The swabs and request form will be pre-labelled with identifying information. Three months after chlamydia diagnosis, the clinic will send an SMS reminder to encourage the patient to either: (i) return to the clinic for retesting; or (ii) collect a sample/s using the collection kit and mail it to the lab with the request slip. A purpose-built database will be used to generate a list of patients due to be mailed home-collection kits. The collection kit will be mailed to the patient in an unmarked envelope by the research team. Patients will be instructed in a covering letter to collect their specimen/s and package them according to the instructions provided and mail them to the laboratory in the pre-paid envelope.

### Control (standard care) arm

Three months after chlamydia diagnosis patients will be sent an SMS reminder by the clinic to encourage them to return to the clinic for retesting. This is routine practice at the two participating clinics.

### Specimen processing, testing and results

#### Chlamydia testing

The baseline chlamydia positive specimens (600) and clinic group retesting specimens will be tested by the clinic’s usual pathology provider. Specimen collection and processing will be in accordance with the pathology provider’s usual protocol, and pathology providers will be requested to store chlamydia positive baseline and retest specimens until the end of the trial. Results will be given to patients according to the clinic’s protocol for managing test results. Treatment for chlamydia positive cases is 1g single dose azithromycin according to the routine practice [25].

All home group retesting specimens will be processed by a specialist laboratory. The laboratory will also be asked to store the specimens until the end of the trial. Results will be reported back to, and managed by the referring clinics, in the usual manner.

#### Serovar detection

Confirmation of each chlamydia serovar, and detection of genotypic variants will be determined by qPCR assay and DNA sequencing [56]. qPCR will be performed in a primary chlamydia group-specific multiplex PCR which utilises two primers and four probes, specific to all chlamydia types, including the B group (B, E, D, L1, and L2), C group (A, C, H, I, J, K, and L3) or intermediate group (F and G) serovars. The primary group-specific PCR will be used to determine which set of secondary serovar-specific PCRs to perform, as described previously [56]. When the same serovar is detected at diagnosis and follow-up, further discriminatory confirmation of relatedness using multilocus sequence typing (MLST) will be conducted [57].

### Outcomes

The primary outcome is the proportion of patients who retest between 1-4 months after a chlamydia diagnosis.

The secondary outcomes are:

1. The repeat positive test rate.

2. Reinfection rate.

3. Acceptability of home testing with SMS reminders.

4. Cost effectiveness of home testing.

### Data collection methods and variables

#### Clinical and sexual behaviour data

Among all patients who test positive at the study site in the recruitment period a range of variables (condom use, number of partners, previous chlamydia diagnoses, anal and uro-genital symptoms, treatment and chlamydia results) will be extracted from the patient management system for all episodes of care during the trial period.

#### Acceptability data

Participants in both study arms will be asked to complete a quantitative survey online. An SMS reminder will be sent to participants at 4.5 and 5 months (after ascertainment of the primary outcome). The SMS will contain the study website and the participant’s code which is linked to their patient details captured at consent. The survey will investigate participants’ living situation (with parents or not), chlamydia treatment for themselves and partners, sexual behaviour, retesting at the same clinic or elsewhere, reasons for not retesting, acceptability of SMS reminders, and for participants in the home group, the acceptability of home testing, ease of collection and retesting preferences (home or clinic retesting). On completion of the survey participants will be sent a $40 AUD voucher, irrespective of retesting. If the participant notes on the online survey that they had a chlamydia test at a clinic other than the sexual health clinic since their positive test, the participant will be mailed a consent form to obtain their permission to contact this clinic to obtain the results of this test. The consent form will then be mailed to the doctor at the clinic.

#### Cost analysis data

The cost of an organised chlamydia retesting program will be assessed from the perspective of the health care provider only. Cost data will relate to patients seen in the 12 months prior to the commencement of the study. De-identified data will be extracted from the patient management system for each patient interaction including: triage time, consultation time, staff type, risk group of client, type of clinic (regular or fast track clinical service known as the express clinic) and number of SMS reminders sent. Where these data are not available through the patient management system, (for example phone times and administration time), log sheets will be developed for the relevant staff members to document the time taken for each interaction.

### Analysis

#### Chlamydia retesting and repeat positive test rates

The final analysis of primary and secondary outcomes will be performed at the conclusion of the trial. Patient baseline characteristics will be compared by randomised group as appropriate but no formal statistical tests will be undertaken. Analyses will be conducted using STATA statistical analysis software. An intention-to-treat approach will be taken.

In the initial analysis, the percentage of individuals who returned will be cross tabulated by randomised group. The analysis will determine the effect of the intervention on primary and secondary outcomes overall and between risk groups (MSM, women and heterosexual men). The primary analysis will be retesting rates between 1-4 months after a chlamydia diagnosis. Per protocol analyses will include: i) among the home-testing arm: the percentage who retested at home compared with the clinic, and the median time to retest among those who tested at the clinic versus home; ii) in each arm: the median time to retest (overall and in those who retested positive); and iii) factors associated with repeat positivity among those who retested at 1-4 months.

#### Reinfection rate

Consistent with the algorithm described by Batteiger [18] repeat positive cases will be discriminated using sexual behaviour data (from the questionnaires and data extracted from the patient management system) and chlamydia genotyping. To differentiate between chlamydia reinfection, treatment failure or persistent infection, we will use a modified version of the chlamydia repeat infection algorithm developed by Batteiger et al. [18] and adapted by Walker et al. [13] (Figure 2). If a participant has two infections with different genotypes, then the second infection will be considered a reinfection. If participants received appropriate treatment but had unprotected sex with their current or new partners, the second infection will also be considered a reinfection. Treatment failure will be defined as a positive chlamydia result following appropriate treatment if the participant reported either no sex between the two episodes or always using condoms with sex. An infection will be defined as persistent if the participant has two consecutive positive chlamydia test results and was not treated between episodes [18,13].

**Figure 2 F2:**
[figure not shown]
**Algorithm to differentiate between chlamydia reinfection, treatment failure and persistent infection (adapted from Batteiger et al. **[18]** and Walker et al. **[13]**).** N/A = Genotype result not available.

#### Acceptability

The acceptability of home-testing in the home group participants will be compared in the three different risk groups using a Chi-2 test, with breakdowns according to age group, sex, symptoms and sexual behaviour. Factors associated with acceptability will be assessed using multivariate logistic regression. The primary outcome of the analysis will be preference for home-testing.

#### Cost analysis

In order to estimate the costs of each component of retesting, a flowchart will be constructed to describe the pathway of patients from their initial chlamydia test, notification of results and treatment, to retest, either at the clinic or via home-based collection, notification of results and treatment. Labour costs will be estimated based on time, staff type and average salary. All equipment for each clinical interaction will be listed and priced according to clinic inventories. The costs of diagnostic testing will be based on the Medicare Benefits Schedule (a listing of the Medicare services subsidised by the Australian government). The cost of clinic and home-based retesting will be compared. The cost of testing at the regular clinic versus the express clinic and between risk groups will also be compared. Using the cost data and primary outcome data of retesting and repeat positive test rates, a cost-effectiveness analysis will be undertaken.

### Data storage

A central database containing de-identified quantitative trial data will be held at the Kirby Institute. All electronic files will be password protected and only the trial research staff and statistician will have access. Participants’ contact details will be securely stored separately to the quantitative trial data.

### Sample size calculation

The sample size is based on a chlamydia retesting rate of 40% in the clinic group (receiving the SMS) based on findings from previous studies. In the analysis we are interested in assessing the primary outcome in the three risk groups (200 MSM, 200 women and 200 heterosexual men) and overall. A sample size of 194 in each risk group will achieve at least 80% statistical power to detect an overall 20% difference (60% compared to 40%) in retesting between home and clinic groups. The 194 will be rounded to 200, and summed up to give an overall sample size of 600. A total sample size of 600 will achieve at least 80% statistical power to detect an overall 12% difference (52% compared to 40%) between home and clinic group for all three risk groups combined. Assuming the retesting rates above are achieved, and the repeat positivity in the clinic group is 10%, we have 80% power to detect an increase of 13% (10% compared to 23%) in repeat positivity.

